#### Quantitative

At the end of the Beacon Site project period, a report will be requested from the NACR team based on the University of York on:

Number of referrals made to the Beacon Sites during the study period.Number of patients with HF enrolled on the REACH-HF programme (attending at least one session).CR attendance (average number of face-to-face and telephone sessions per patient).Number of patients completing the REACH-HF programme (in the clinical trial^11^ patient adherence was defined as attendance at the first face-to-face contact with the facilitator and at least two facilitator contacts thereafter—at least one of which must have been face-to-face).

Summary data on key pre and post-programme measures will also be requested to enable comparison with changes in the intervention group observed in the clinical trial. These include HRQoL—determined using the MLHFQ and exercise capacity—determined using the ISWT. The MLHFQ consists of 21 questions that rate on a scale of 0–5 (where 0 is not at all, 1 is very little and 5 is very much) how different HF symptoms (ie, swelling of ankles and legs, shortness of breath or tiredness, fatigue and poor energy levels) prevent the patient from living as they would have wanted to during the 4-week period prior to the first CR session. ISWT is an externally paced exercise capacity test that can be administered in the field with minimal equipment and without medical supervision. The test has good test–retest reliability and it is an acceptable alternative to (widely used to assess physical fitness and functional capacity of cardiac patients) exercise test with ECG monitoring or the cardiopulmonary exercise test.^32^ A recent study confirmed that a single ISWT is a valid, low resource, assessment of an estimate for physical fitness and functional capacity for CR patients.^33^

### Data analysis

#### Qualitative data

Digital recordings of interviews and focus groups will be transcribed verbatim and any potentially identifiable information, such as individual or location names, will be redacted. The transcripts (Word documents) will be uploaded into NVivo software to help organise the data for analysis.^34^ Illustrative quotes, that may be used in future presentations or publications, will be presented alongside pseudonyms to protect anonymity.

The transcripts will be analysed according to the principles of framework analysis outlined by Ritchie and Spencer^35^ and using the four over-arching constructs of NPT (coherence, cognitive participation, collective action and reflexive monitoring) as an initial framework for coding the data.^36^ NPT suggests general mechanisms that are associated with successful implementation. These include service providers’ understanding of the new intervention and how it differs from standard practice, their motivation and attitude towards the healthcare innovation and the work they do to deliver and evaluate the intervention. NPT will provide a framework for generating questions for interviews and focus groups and analysing gathered data. See table 1 for more details on the application of NPT to the data collection.

#### Fidelity assessment

Implementation fidelity scores from the fidelity checklist will be collated at the level of the facilitator, the site and the total sample and presented using descriptive statistics (means, ranges) using the same analytic approach as the original REACH-HF trial.^11^ Numerical data (0–6) from the Dreyfus scale of clinical skill acquisition will be converted into categorical (yes/no) data reflecting whether the session reached the adequate level of delivery (score 3 or above). Observer-rated treatment fidelity will be compared with self-rated fidelity from the post-session fidelity questionnaires completed by the REACH-HF facilitators at the end of each recorded session. The analytic approach to compare the two rating scales will be Pearson’s correlation for continuous scores^37^ and Gwet’s first-order agreement coefficient (the AC1 statistic) for categorical ratings.^38^

The fidelity assessment data sample reflects the sample size used to assess fidelity in the original REACH-HF clinical trial. We require a minimum of four patient recordings per facilitator to be able to assess variation in performance between staff and between NHS sites.

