#### Fidelity assessment

All REACH-HF CR treatment sessions (four–six contacts), both face-to-face and phone-based, of approximately 48 consenting patients (12 per site), will be audio recorded by the healthcare professionals delivering the programme. Each REACH-HF facilitator will be requested to audio record all treatment sessions for four patients with HF. The selection of which patients to include will be guided by the researchers, using a quasi-random process. Five months after the REACH-HF training, facilitators will be asked to invite all subsequent patients to take part in the study, until two willing patients with HF agree to have their treatment sessions recorded. Approximately 10 months after the REACH-HF training, an email will be sent to repeat the invitation and audio recording process for the next two consenting patients.

The quality of delivery (intervention fidelity) of the recorded treatments will be assessed by the researcher (PD) using the same fidelity checklist used in the original REACH-HF research study.^11^ This will allow comparison with fidelity scores achieved in the clinical trial. The recordings for the first six patients will also be double scored and two researchers (PD and CG) will discuss any differences in their scores to agree and ‘anchor’ the scoring process and minimise coder bias. If an agreement cannot be reached, a third reviewer ([name]) will be appointed for arbitration.

The fidelity checklist is a 12-item checklist focused on identifying key delivery processes such as the use of a patient-centred communication style, making a plan of action and encouraging self-monitoring of progress (particularly with the exercise programme). The checklist uses the Dreyfus scale of clinical skill acquisition,^31^ to rate clinical skills on a scale of 0–6 and is anchored such that a score of 3 or more represents adequate delivery quality for each item. Coding instructions are provided (online supplementary appendix 2).

10.1136/bmjopen-2019-036137.supp2Supplementary data

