REACH-HF facilitators will be asked to complete a brief self-rated fidelity checklist after each session they have recorded. This comprises questions about the same 12 main components of the treatment and allows the facilitators to rate the occurrences of each feature (absence, minimal, some, sufficient, good, very good, excellent) (online supplementary appendix 3). The main reason for including a self-rated fidelity checklist is that an independent observer rating is time-consuming/labour intensive, whereas a self-rating assessment might provide a pragmatic, lower cost alternative for checking delivery quality for use in real-world clinical practice.

10.1136/bmjopen-2019-036137.supp3Supplementary data

Finally, for each patient opting into the study, age, sex, time since diagnosis and severity of symptoms will be recorded by the healthcare professionals delivering the REACH-HF intervention.

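### Self-rated fidelity is proposed as a cheaper substitute for observer rating, but Pearson's r cannot show inflated self-ratings, and AC1 can stay high while poor sessions go undetected if such sessions are few

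*Protocol article*

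**What the plan says.** Under Measures and procedures, Fidelity assessment, the protocol article describes two ratings of each recorded session on the same 12 components. The observer scores each item from 0 to 6, and the scale is "anchored such that a score of 3 or more represents adequate delivery quality for each item". After each recorded session the facilitators "rate the occurrences of each feature (absence, minimal, some, sufficient, good, very good, excellent"), which is seven ordered labels. The main reason given for the second rating is that "a self-rating assessment might provide a pragmatic, lower cost alternative for checking delivery quality for use in real-world clinical practice".

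Under Data analysis, Fidelity assessment, the comparison is fixed in two parts. For scores: "The analytic approach to compare the two rating scales will be Pearson’s correlation for continuous scores". For the adequate/inadequate version, the 0 to 6 scores are "converted into categorical (yes/no) data reflecting whether the session reached the adequate level of delivery (score 3 or above"), and the statistic is "Gwet’s first-order agreement coefficient (the AC1 statistic) for categorical ratings".

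For this comparison the article names no self-minus-observer difference, no limits of agreement, no absolute-agreement coefficient, and no sensitivity or specificity of self-rating. Checklist scores are to be summarised as means and ranges, but the text does not say that self-rated means will be set beside observer means.

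**The concern.** If self-rating is to stand in for observer rating, two things must be known: whether the self-score lies at the right level, and whether it picks out the sessions an observer would call inadequate. Over-rating one's own work is an obvious possible error, and Pearson's r is blind to its constant part. AC1 does respond to inflation that crosses the cut. When nearly all sessions are adequate, however, the adequate/adequate cell dominates it, and a self-rating that flags almost nothing still scores well.

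Both named statistics could therefore look strong for a tool that overstates quality and misses most poor sessions. A service that relied on them to choose self-rating as its quality check would be misled.

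A smaller point concerns the cut. It is anchored per item in the first section and worded per session in the second, so the unit of the 2x2 table is not clear.

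**Working it through.** **The plan's own numbers.** 4 sites × 3 facilitators × 4 patients = 48 patients, as stated. With four to six contacts each, this gives 48 × 4 = 192 to 48 × 6 = 288 paired ratings from 12 facilitators. The article states no expected agreement, score distribution or share of inadequate sessions.

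**Pearson.** Let O be the observer score and S the self-score. Cov(O, S + c) = Cov(O, S) and the SDs do not change, so r is the same for any constant c, as long as the top of the scale does not bind. If S = O + 1 exactly, r = 1.00. This does not depend on how many sessions are inadequate.

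**Illustration.** All values are assumptions: O and S bivariate normal, observer mean 4.0, self mean 5.0, both SDs 0.8, r = 0.80, cut at 3, self-rating labels read as 0 to 6.

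- Observer-inadequate: Φ((3 − 4)/0.8) = Φ(−1.25) = 0.106.
- Self-inadequate: Φ((3 − 5)/0.8) = Φ(−2.5) = 0.006.
- Both inadequate, from the bivariate normal distribution: 0.0059.
- Sensitivity of self-rating for inadequate sessions: 0.0059/0.1056 = about 6%. It cannot exceed 0.0062/0.1056, also about 6%.
- Observed agreement: pa = 1 − (0.1056 − 0.0059) − (0.0062 − 0.0059) = 0.900.
- Mean proportion adequate: π = 1 − (0.1056 + 0.0062)/2 = 0.944. Chance term: pe = 2π(1 − π) = 0.106.
- AC1 = (0.900 − 0.106)/(1 − 0.106) = 0.89.
- Covariance = 0.80 × 0.64 = 0.512. Absolute-agreement ICC = 0.512/(0.64 + 1²/2) = 0.512/1.14 = 0.45. Lin's concordance = 2 × 0.512/(0.64 + 0.64 + 1²) = 0.45.
- SD of the difference = √(0.64 + 0.64 − 1.024) = 0.51, so the limits of agreement are 1 ± 1.96 × 0.506, about 0.0 to 2.0 points.

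Truncating the scores at 0 and 6 in a simulation of the same model gives r = 0.79, mean difference 0.96 and concordance 0.44, so the ceiling does not change the picture.

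**The same model without inflation.** With the self mean at 4.0, the joint probability of both inadequate is 0.060. Sensitivity is 0.060/0.1056 = 57%, pa = 1 − 2 × (0.1056 − 0.0600) = 0.909, pe = 2 × 0.894 × 0.106 = 0.189, and AC1 = (0.909 − 0.189)/0.811 = 0.89. Both planned statistics are the same to two decimals for a tool that flags 57% of inadequate sessions and one that flags 6%.

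**How far the AC1 part reaches.** If a share f of sessions is inadequate and self-rating flags none, then pa = 1 − f, π = 1 − f/2, and AC1 = (1 − 2f + f²/2)/(1 − f + f²/2).

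| f | AC1, none flagged |
|---|---|
| 5% | 0.901/0.951 = 0.95 |
| 10% | 0.805/0.905 = 0.89 |
| 20% | 0.620/0.820 = 0.76 |
| 30% | 0.445/0.745 = 0.60 |
| 40% | 0.280/0.680 = 0.41 |

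A second simulation (240 sessions, observer SD 0.9, self-rating inflated by 1.5 points with error SD 0.45, scores held within 0 to 6; all assumed) shows the two parts separately:

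| Inadequate | r | AC1 | Inadequate sessions flagged |
|---|---|---|---|
| 9% | 0.82 | 0.90 | 4% |
| 19% | 0.85 | 0.79 | 6% |
| 29% | 0.87 | 0.64 | 8% |
| 50% | 0.89 | 0.27 | 14% |

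r stays high throughout, while AC1 gives warning once inadequate sessions are common.

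**The case against.** The strongest reply is about weight. The four objectives concern barriers and facilitators, delivery quality, adaptations, and outcomes compared with the trial. Delivery quality is judged from the observer's checklist, so nothing here alters a main result. The wording on substitution is tentative, and no threshold or rule for adopting self-rating is given. All of this stands and limits the importance of the point. A reader might infer that the plan would lead to self-rating being endorsed nationally; the documents do not go that far.

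The second reply is that AC1 is a legitimate agreement coefficient and does not leave the plan resting on Pearson alone. That also stands in part: AC1 falls clearly once inadequate sessions reach about 30% or more. It does not rescue the case where they are few, and the documents give no reason to rule that case out.

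The third reply is that a condensed article need not list every table. This does not stand, because the article states the analytic approach for this comparison, and the approach does not match the stated purpose.

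Two stronger readings are tempting. One is that the plan averages the 12 items, so that high items hide undelivered ones. The text does not say so; it leaves open how the cut is applied. The other is that the plan's intervals ignore clustering within facilitators. It states no interval for r or AC1, so there is nothing to criticise, only a precaution to take.

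**Conclusion.** The concern holds in limited form. The Pearson part is a mathematical fact: the statistic named for the continuous comparison cannot reveal a constant over-rating at any share of inadequate sessions. The AC1 part is conditional. With nothing detected, AC1 is about 0.89 at 10% inadequate, but about 0.76, 0.60 and 0.41 at 20%, 30% and 40%. Under the illustrative assumptions, r = 0.80 and AC1 about 0.89 go with an ICC of about 0.45 and about 6% of inadequate sessions flagged. The mean, SD, shift, correlation and share inadequate are all assumed, since the documents give none of them. The unit of the cut is an ambiguity to be resolved, not a shown error. The plan should be corrected, but the analysis is subsidiary and the main fidelity assessment is unaffected.

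**What to change.** In Data analysis, Fidelity assessment:

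- For scores, make the mean self-minus-observer difference with limits of agreement, together with an absolute-agreement ICC or Lin's concordance, the main comparison. Keep Pearson's r as a secondary description.
- For the yes/no ratings, keep AC1. Report beside it the 2x2 table, with sensitivity and specificity of self-rating for observer-rated inadequate delivery.
- State whether the cut of 3 is applied to each item, as it is anchored, or to the session, as the analysis section words it; if to the session, state how the 12 items are combined.
- State how the seven self-rating labels map to 0 to 6.
- If intervals are reported, allow for sessions nested within 12 facilitators, for example by resampling facilitators.

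The same paired ratings serve for all of this, so no new data are needed. The cost is a little more analysis, and reported agreement may look less favourable. If few sessions are inadequate, sensitivity will be imprecise, and the counts should be shown.

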#### Quantitative outcomes

Changes from pre to post-treatment in outcome data (MLHFQ and ISWT) will be reported as mean scores with 95% CI within each Beacon Site. Mean change scores for patients receiving REACH-HF will be compared across Beacon Sites and also with the changes found in the REACH-HF trial. This comparison will take account of potential differences on patient characteristic and take due attention to the confidence intervals. Similarly, change scores for patients receiving REACH-HF will be compared with an aggregate change score from the NACR database for those who receive other forms of CR (primarily centre-based or digital CR). Subgroup analyses will be conducted by the NACR team to determine variations in uptake and outcomes within our REACH-HF cohort by site, sex and other characteristics of interest (eg, area deprivation index, rurality). Data on the number of patients treated, uptake and completion rates and session attendance, will be presented using descriptive statistics. Figure 2 illustrates the interactions between the study’s aims and methods and how they link with the process of ongoing evaluation and scale-up.

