**Ethics and dissemination:**

The study (IRAS 261723) has received ethics approval from the South Central (Hampshire B) Research Ethics Committee (19/SC/0304). Written informed consent will be obtained from all health professionals and patients participating in the study. The research team will ensure that the study is conducted in accordance with the Declaration of Helsinki, the Data Protection Act 2018, General Data Protection Regulations and in accordance with the Research Governance Framework for Health and Social Care (2005). Findings will be published in scientific peer-reviewed journals and presented at local, national and international meetings to publicise and explain the research methods and findings to key audiences to facilitate the further uptake of the REACH-HF intervention.

Strengths and limitations of this studyThis will be the first study to investigate the real-world implementation of a home-based cardiac rehabilitation programme in the UK and also to include the evaluation of the real-world clinical effectiveness of the programme.The study will use Normalisation Process Theory as a theoretical framework to guide data collection and interpretation.The qualitative findings will inform the development of an implementation manual for policymakers, planners, providers and commissioners of cardiac rehabilitation services for patients with heart failure.A possible limitation of the study is that the four centres that will be appointed to implement the REACH-HF programme are large, well-established cardiac rehabilitation treatment centres and might not be representative of the national cardiac rehabilitation landscape—a potential sample bias towards early adopters.This study may have limited generalisability outside the UK.

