### Setting and site recruitment

The study will be conducted in four UK NHS CR centres (desirably from the four UK countries) which will be early adopters of the REACH-HF programme and known as ‘Beacon Sites’. The opportunity to apply to become a Beacon Site will be promoted at national (UK) conferences and local meetings of CR practitioners. Interested CR services will be sent an information pack including an application form. Applicants will be asked to provide information on their NACR National Certification Programme for CR status (NCP_CR), number of referrals made to the CR service (for both cardiac patients and patients with a primary diagnosis of HF), whether the service is offering home-based programme, length of current programmes, number of programme completions, number of pre and post-treatment assessment completions, as well as to comment on willingness to engage in research and host site visits for other interested parties.

The NCP_CR is a national certification programme for CR issued jointly by the British Association for Cardiovascular Prevention and Rehabilitation (BACPR) and the NACR. The certification programme rates CR services on seven key performance indicators (KPIs). KPIs are the NACR measurable indicators based on the BACPR core components. Programmes need to meet at least four KPIs to be granted an amber status and all seven to be granted a green status (2019 NACR Quality and Outcomes report).

The sites will be recruited from across the UK using a two-stage application process (application form followed by panel interview for shortlisted sites). As an incentive, sites will be offered free intervention materials for the treatment of 50 patients (ie, the REACH-HF patient manual, the Family and Friends Resource, audio with relaxation techniques and chair-based exercise digital versatile disc (DVD)). In addition, the selected sites will be offered free training (including training manuals) for three health professionals to deliver REACH-HF, post-training support and formative feedback on performance. The 3-day training will be delivered by the Heart Manual Department (HMD), NHS Lothian in Edinburgh.

To be eligible, sites have to be:

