NACR electronically registered sites with high-quality status from the past audit period (green or amber status) operating in the UK.Committed to delivering REACH-HF to 50 patients over the 12-month Beacon Site project period.Able to release three healthcare professionals (or more) with relevant experience in CR and/or HF for 3 days training plus one self-directed pretraining day.Able to engage in research to evaluate performance (ie, recording some intervention sessions and staff participation in interviews).Willing to host site visits and/or share information and/or experiences with other interested NHS parties.Conduct baseline and post-treatment assessment of HRQoL using the Minnesota Living with Heart Failure Questionnaire (MLHFQ)^25^ and exercise capacity using the Incremental Shuttle Walk Test (ISWT)^26^ for all patients receiving the REACH-HF programme.

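### The supplementary contrast with the NACR aggregate sets competitively selected green or amber sites against a comparator with no stated site restriction, so it cannot separate programme from site selection

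*Protocol article*

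**What the plan says.** **How the REACH-HF sites are chosen** (protocol article, Setting and site recruitment). Eligible sites are "NACR electronically registered sites with high-quality status from the past audit period (green or amber status) operating in the UK". The section defines the status levels: "Programmes need to meet at least four KPIs to be granted an amber status and all seven to be granted a green status". Recruitment is in two stages, "application form followed by panel interview for shortlisted sites". The form asks, among other things, for "number of programme completions, number of pre and post-treatment assessment completions". Sites must also undertake to measure MLHFQ and ISWT before and after treatment in every REACH-HF patient.

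**What they are compared with** (Quantitative outcomes). Mean changes are compared across Beacon Sites and with the trial, taking account of differences in patient characteristics. The next sentence adds that REACH-HF change scores will be "compared with an aggregate change score from the NACR database for those who receive other forms of CR", mainly centre-based or digital programmes.

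**What is acknowledged** (strengths and limitations list after the abstract). It says that "the four centres that will be appointed to implement the REACH-HF programme are large, well-established cardiac rehabilitation treatment centres", that they may not represent national services, and that the sample may lean towards early adopters.

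**The concern.** In this contrast the programme and the kind of service delivering it change together. One side comes only from services that passed a quality threshold and then a competitive selection. The other side is described only by the type of rehabilitation received. If services of that kind achieve different changes in MLHFQ or ISWT whatever programme they run, the difference enters the contrast and looks like a programme difference.

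The protocol's own introduction gives a reason to expect this. It says that an intervention can perform differently between organisations because of their resources, staff and expertise.

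The study is presented as including an evaluation of real-world effectiveness, and its results are to inform national roll-out. A commissioner could easily read REACH-HF against centre-based or digital rehabilitation as a comparison of programmes.

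**Working it through.** The documents give no sample size, effect size or margin for this contrast, so there is no figure to reproduce. The check is of structure.

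**1. The two sides as written**

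| Feature | REACH-HF side | NACR comparator |
|---|---|---|
| Certification | Green or amber required (at least 4 of 7 KPIs) | No restriction stated |
| Further site selection | Application form, shortlisting, panel interview | None stated |
| Number of services | Four | Not stated |
| Stated filter | Received REACH-HF at a Beacon Site | Received another form of rehabilitation |
| Adjustment | Patient characteristics at most | Patient characteristics at most |

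The adjustment sentence comes before the NACR sentence and refers to the comparisons across sites and with the trial. Even if it is read as carrying over, it does not cover site characteristics.

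**2. What the contrast estimates**

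Let τ be the programme difference and let s be the average contribution of the service to the change score, whatever the programme: s_B for the Beacon Sites, s_GA for all green or amber programmes, s_N for the services in the aggregate. Leaving patient mix aside:

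- National aggregate: τ + (s_B − s_N) = τ + (s_B − s_GA) + (s_GA − s_N)
- All green or amber programmes: τ + (s_B − s_GA)
- Same four sites: τ + a, where a is the effect of how each site allocates patients between REACH-HF and other rehabilitation

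The certification-matched comparator removes one of the two site terms. The same-site comparator removes both but adds a. Neither gives τ alone, which is why they are worth reading together.

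**3. Why sample size does not help (illustration, not an estimate)**

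Assume τ = 0, n = 200 (4 sites × 50 patients, the stated maximum), the aggregate treated as fixed, and no clustering by site. Let δ = s_B − s_N in SD units of the change score. The values of δ are assumed; no document supports any of them.

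SE = 1/√200 = 0.071 SD. The probability that the 95% CI excludes zero is 1 − Φ(1.96 − δ/SE) + Φ(−1.96 − δ/SE).

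| Assumed δ (SD) | δ/SE | Probability |
|---|---|---|
| 0 | 0 | 0.05 |
| 0.05 | 0.71 | 0.11 |
| 0.10 | 1.41 | 0.29 |
| 0.20 | 2.83 | 0.81 |
| 0.30 | 4.24 | 0.99 |

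The formula is symmetric, so a shift of the same size against REACH-HF gives the same probabilities. More patients reduce the SE and leave δ unchanged.

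**The case against.** The strongest reply is that this is one descriptive sentence. Aim 4, and the Design section's stated use of NACR data, concern the comparison with the trial. The NACR contrast has no hypothesis, test or decision rule, and nothing says that a difference will be credited to REACH-HF. That stands, and it limits the weight of the point. It does not make the comparator a good choice for the reading that the contrast invites.

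Three stronger readings are tempting, and the documents do not support them:

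- **That the aggregate is known to contain uncertified services, or to leave out the Beacon Sites' own patients.** Only the lack of a stated restriction is on the page. As worded, Beacon Site patients on other rehabilitation would fall inside the aggregate. A fuller protocol or analysis plan may set filters.
- **That sites are selected for completing assessments.** Applicants report "number of pre and post-treatment assessment completions", but no threshold or scoring rule is given, and the MLHFQ and ISWT requirement is a forward commitment. It bears on missing outcome data, not on a stated quality criterion.
- **That the bias favours REACH-HF by some amount.** No passage links certification to change scores. Amber needs only four of seven KPIs, so the gap may be modest, and a ceiling effect could reverse the sign.

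The authors can also say that they disclose a possible sample bias towards early adopters. They do, as a matter of how representative the sites are. They do not connect it with this contrast, and the disclosure changes nothing in the comparison itself.

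Finally, neither replacement comparator is free of bias. That is correct, and it is a reason to report them beside the national aggregate and not in its place.

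**Conclusion.** The point holds in a limited form. As written, the supplementary contrast cannot separate programme from site selection, because the REACH-HF side is restricted by certification and competition, the comparator has no stated site restriction, and any adjustment is for patient characteristics only. The conclusion rests on the article's text; a restriction in a document not shown would narrow it. Size and direction cannot be derived, and the SD-unit illustration shows only how an assumed shift would behave. The trial comparison under aim 4 is not affected by this point. It is a low-cost improvement worth making before the final NACR request, not a flaw that threatens the study.

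**What to change.** In the NACR data request, keep the national aggregate and add change scores for patients on other forms of rehabilitation from:

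1. all green or amber programmes over the same calendar period as the Beacon Site project; and
2. the same four Beacon Sites over that period, where numbers allow.

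Report all three side by side, with the certification-matched comparator taking precedence. Add to Quantitative outcomes a statement such as: *This contrast is descriptive; differences may reflect the selection of Beacon Sites as well as the programme.*

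**Cost.** Two additional extracts and one or two sentences. The final download is requested only when Beacon Site activity ends, and the interim one stops short of analysis, so the change can be made before results are seen. Certification is issued jointly with NACR, so status should be available as a filter, but the documents do not confirm that change scores can be supplied this way; NACR should be asked.

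**Downside.** The same-site comparator will be smaller, with a wider interval, and depends on how sites allocate patients between programmes. The certification-matched comparator leaves the effect of competitive selection among certified sites.
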